## Data collection and management

### Plans for assessment and collection of outcomes {18a}

A detailed data management plan will be developed to outline the data management processing, data cleaning and QC procedures for the trial. The data management aspects of the study are summarised here:

#### Source data

Source documents are where data are first recorded and from which participants’ CRF data are obtained. These include, but are not limited to, hospital records (from which medical history and previous and concurrent medication may be summarised into the CRF), clinical and office charts, laboratory and pharmacy records, diaries, microfiches, radiographs, and correspondence.

CRF entries will be considered source data if the CRF is the site of the original recording (e.g. there is no other written or electronic record of data). All documents will be stored safely in confidential conditions. On all trial-specific documents, other than the signed consent, the participant will be referred to by the patient trial ID, not by name.

#### Monitoring

Regular monitoring will be performed according to the trial specific monitoring plan. Data will be evaluated for compliance with the protocol and accuracy in relation to source documents as these are defined in the trial specific monitoring plan. Following written standard operating procedures, the monitors will verify that the clinical trial is conducted and data are generated, documented and reported in compliance with the protocol, GCP and the applicable regulatory requirements.

#### Local investigator and site personnel training

All key site personnel must undergo relevant training in advance of the site initiation in accordance with Good Clinical Practice (GCP) guidelines. Such training will be documented. In addition, training for site staff will be provided by OrganOx Ltd. in advance of recruitment of the first patient. A record of all device training will be maintained. All personnel involved in randomisation and data entry will also be trained in the use of the online randomisation and data collection tool by members of the clinical trials unit, and records of such training will be maintained.

#### Study documentation

It is the responsibility of the local investigator to maintain complete, accurate and current study records. Each investigator will be provided with an investigator site file, online access to the case reporting system and other associated study specific documentation by the co-ordinating centre. Such records will be maintained during the course of the study and for up to 5 years following the date on which the study is terminated or completed, in accordance with local regulatory requirements.

### Plans to promote participant retention and complete follow-up {18b}

The follow-up visits for the DeFat study align with routine clinical visits. All patients completing the 6-month follow-up assessment will be regarded as having completed the primary study. All patients will be encouraged to complete study follow-up, and all reasonable efforts will be made to ensure completeness of follow-up. Measures include ensuring that sample collection and assessments are made, where possible, at routine hospital visits rather than additional appointments and that patients do not incur extra financial costs (e.g. travelling costs) as a result of study participation.

It is understood that study participants may withdraw consent for study participation at any time irrespective of their reasons. The investigators may also withdraw a recipient from the study in order to protect their safety and/or if they are unwilling or unable to comply with the required study procedures. We will keep all data accrued to the point of withdrawal, as is stipulated in the trial consent form.

Possible reasons for investigator-led withdrawal of a participant from the trial include:Major protocol deviationWithdrawal of consentLoss to follow-upSAE/SUSAREarly termination of study

In the event of a patient withdrawing from the trial, the reason for withdrawal must be documented on the eCRF. Such patients will be asked whether they consent to the use of ongoing data collected as standard in the national transplant registry for the purposes of this study.

### Data management {19}

#### Data recording and record keeping

Randomised liver and participant data will be entered onto the trial database designed and administered by the NHSBT CTU data management team using MACRO™, a commercially available FDA 21 Code of Federal Regulations (CFR) Part 11 compliant clinical trial database system produced by InferMed. Following completion of analysis, the trial database will be archived in accordance with NHSBT’s policies.

The study team must keep the signed informed consent forms, all trial documentation and source documents collected during the trial in a secure location (e.g. locked filing cabinets in a room with restricted access). All data must be accessible to the competent authorities and the sponsor with suitable notice for inspection.

The participants will be identified by a unique patient trial ID in any database. Participant identifiers (e.g. NHS number) will only be stored where required for linkage to external data sources (e.g. NHSBT). Individual participants will not be identified in the resulting publications and presentations from the trial. This trial will comply with the UK Data Protection Act (2018) and the General Data Protection Regulation

All trial documentation must be retained for at least 5 years after trial completion or termination. In addition, the investigator must not discard or destroy any trial specific materials unless otherwise instructed by NHSBT.

#### Use of registry data

The UK Transplant Registry will be the primary source of data about resource use (hospital stay and reasons for re-admission), biochemistry results (liver and renal function), transplant-related renal dysfunction and graft/patient survival at 12 months. Where available, the primary source of recipient outcome data will be that collected from the electronic case report forms. Where primary or secondary outcome data are missing, we will attempt to link to the NHS Blood and Transplant registry to obtain missing data where recorded. The primary source for 12 months outcome data will be the UK Transplant Registry. Linkage between trial and registry data will only be undertaken by statisticians working on the trial and registry identifiers will be removed from datasets after linkage has been undertaken. NHS Blood and Transplant Information Governance have conducted a Data Protection Impact Assessment, are satisfied that confidentiality and data protection measures are in place and approved the use of UK Transplant Registry Data for this study.

### Confidentiality {27}

The study will comply with the General Data Protection Regulation (GDPR) and Data Protection Act 2018, which require data to be de-identified as soon as it is practical to do so. The processing of the personal data of both donors and recipients will be minimised by making use of unique liver and patient trial IDs only on all study documents and any electronic database(s). All documents will be stored securely and only accessible by study staff and authorised personnel. The study staff will safeguard the privacy of participants’ personal data.

### Plans for collection, laboratory evaluation and storage of biological specimens for genetic or molecular analysis in this trial/future use {33}

The trial co-ordinator (clinical research fellow) and/or member of the central trial team will be responsible for collection of perfusate and peri-operative samples.

Perfusate samples will be collected at baseline (pre-NMP) and during preservation (1, 2, 4 and 6 h and at the end of perfusion). Blood samples will also be collected peri-operatively before transplant and post-reperfusion. Three samples will be taken at each timepoint:1× EDTA separator tube (or universal tube if EDTA not available)1× Serum separator tube1× Streck tube for measurement of cfDNA

To ensure minimal sample degradation and pre analytical variability, perfusate and peri-operative samples should be kept at room temperature prior to separation of plasma from cellular parts. Separation of cells from plasma and serum should be achieved by centrifugation at 1500*g* for 10 min at room temperature as close as possible to blood collection. After centrifugation, plasma and serum samples should be kept at 4°C. The perfusate samples will be transferred into 1.0–2.0-mL aliquots and subsequently transported to Oxford University Hospitals NHS Foundation Trust and stored frozen at −80 °C.

In addition to perfusate and peri-operative measurements, cfDNA will also be measured post-operatively. Samples will be collected from recipients in Streck tubes on days 1, 3, 7 and 14 (if discharged before day 14, a sample will be collected on date of discharge). These post-operative samples will be taken by the clinical team at each liver transplant centre and collection will align with routine clinical samples. Follow-up measurements will align with clinic visits on day 30, months 3 and 6. The Streck tubes are stable at room temperature for up to 7 days and will be shipped to an accredited laboratory in the United Kingdom (UK) or abroad.

Bile (if produced) will be collected at 1, 2, 4 and 6 h and at the end of perfusion and transferred into 1.0–2.0-mL aliquots for subsequent transport to Oxford University Hospitals NHS Foundation Trust and stored frozen at −80 °C.

Liver and bile duct biopsies will be taken before perfusion, at the end of perfusion and following reperfusion in the recipient (prior to skin closure). A total of five core liver biopsies will be taken: two biopsies before perfusion, two at the end of perfusion and one following reperfusion. Each liver biopsy will be divided into two segments. Per liver, one segment will be stored in formalin and the remaining segments will be frozen. A single bile duct biopsy will be taken at each timepoint where feasible, i.e. if sufficient length on the bile duct. The bile duct biopsies will not be divided into two and only stored in formalin. The formalin samples will be stored at Oxford University Hospitals NHS Foundation Trust. Frozen samples will also be stored at this location at −80 °C.

Pre-implantation research biopsy samples will only be taken where donor family consent to research is in place. Sample collection will follow national regulations and standard operating procedures. Following collection, storage and transportation will be in accordance with the Human Tissue Authority guidelines and Trust policies. The trial team will have access to the samples and will ensure storage at Oxford University Hospitals NHS Foundation Trust. All research samples will be stored for future research and the mechanistic studies described in the study protocol.

Overall, the trial ID will be used as an identifier for all stored samples. Only personnel authorised by the chief investigator will be responsible for the storage, access and release of these samples for analysis.

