
Histological and biochemicalCorrelation of pre-perfusion donor biopsy (histopathologist’s steatosis report) with:aWC, BMI and clinical risk scores such as the fatty liver index (FLI) and hepatic steatosis index (HSI) [67, 68] where relevant data availablebSurgeon’s assessment [57]cNon-invasive pocket-sized micro-spectrometer reading. The device has been developed by SCIO - Consumer Physics (http://www.consumer-physics.com) and is CE marked. It utilises spectroscopy (absorption of near infrared light, 700–1100 nm). The commercially available device is able to quantify composition of foods, estimate body fat levels and identify analgesic agents [69]. Readings will be taken sequentially over perfusion (where feasible): at baseline (pre-NMP) and during preservation (1 and 6 h and end of perfusion) to facilitate correlation with post-perfusion (end-NMP) biopsy in addition to the pre-perfusion biopsy.Histological and biochemical evidence of ischaemia–reperfusion injury (IRI):aHistology (formalin fixed paraffin embedded) [33]:(i)Neutrophil infiltration and leucocytosis determined using haematoxylin and eosin (H&E) stain(ii)Glycogen depletion determined using periodic acid-Schiff (PAS) stain(iii)Lipid peroxidation determined using 4-HNE (4-hydroxynonenal) stain

Biopsy samples collected pre-perfusion, post-perfusion and re-perfusion in the recipient (following liver transplantation).
bCytokine profile  implicated in liver transplantation including [70]: CXCl8/IL-8, IL-10, IL-2, TNF-a, IFN-γ, IL-13, IL-4, IL-1β, IL-17A and IL-6.

Blood samples collected peri-operatively (before transplant) and re-perfusion in the recipient (following liver transplantation).

3.Histological and biochemical evidence of bile duct injury (BDI) and biliary viability [71] such as:aHistology (formalin-fixed paraffin embedded) biopsy samples pre-perfusion, post-perfusion and following re-perfusion in the recipient (following liver transplantation). For example, evidence of stromal necrosis, loss/injury to peribiliary glands and vascular lesions. Bile duct biopsies will only be taken if sufficient length on the bile duct and feasible to do so.bBile composition measurements (if produced and measured at 1, 2, 4 and 6 h and end of perfusion) for example: low pH and bicarbonate with high glucose and lactate dehydrogenase (LDH) as indicators of poor biliary viability.

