#### Mechanistic studies outcome measures

The identification of novel markers could augment current practice by predicting the outcome of each liver with objectivity. The mechanistic studies will test hypotheses based on previous published studies that have investigated markers in the field of NMP and will inform development of functional criteria and optimisation of future defatting protocols:To measure the effect of the intervention on the histological degree of steatosis:Histological quantification of MaS measured pre-perfusion, post-perfusion and during re-perfusion in the recipient. We hypothesise that the intervention of defatting will reduce the degree of MaS and severity of NAFLD activity score [75].To measure the effect of the intervention on markers on of hepatic lipid metabolism:Perfusate TG, insulin, ketone bodies and cytokines associated with IRI will be measured at baseline (pre-NMP) and during preservation (1, 2, 4 and 6 h and end of perfusion). Further measurements taken from the recipient peri-operatively (before transplant) and re-perfusion (following liver transplantation). This will provide insight into changes in intrahepatic lipid handling and inflammation. We hypothesise that the intervention of defatting will ‘repartition’ intrahepatic fatty acids away from esterification into oxidation pathways leading to a decrease in IHTG and a decrease in IRI-associated cytokine production [70].Perfusate FGF-21 will be measured at baseline (pre-NMP) and during preservation (1, 2, 4 and 6 h and end of perfusion). Further measurements taken from the recipient peri-operatively (before transplant) and re-perfusion (following liver transplantation). FGF-21 is a hormone produced in the liver involved in energy homeostasis; its secretion is attributed to metabolic stress. There is evidence that serum FGF-21 is a useful marker for steatosis and correlates with increasing steatosis grade [76]. We hypothesise that the defatting intervention will reduce FGF-21.To understand the structural, cellular and metabolic effects of defatting on steatotic livers.Genomic analysis of samples taken pre-perfusion, post-perfusion and following re-perfusion in the recipient:◦Transcriptomics: a complex signalling cascade regulates metabolic processes within the liver. To understand the effect of NMP and the defatting intervention, genomic analysis of liver tissue will be undertaken. We hypothesise that the defatting intervention will lead to downregulation in pathways related to fat synthesis and inflammation and an upregulation in pathways related to fat disposal. Samples from livers will undergo RNA sequencing of the liver and this will be correlated with clinical outcomes. Changes in gene expression will be mapped with changes occurring in biological pathways, inferring biological changes during NMP.Proteomic and glycomic analysis of perfusate samples taken at baseline (pre-NMP) and during preservation. Further measurements taken from the recipient peri-operatively (before transplant) and re-perfusion (following liver transplantation):◦Proteomics: a recent study investigating the use of NMP to increase utilisation of high-risk donor livers, identified protein clusters that were able to discriminate between transplantable and non-transplantable livers (22 out of 31) as well as markers predictive of post-transplant complications [77]. We aim to determine the effect of the intervention on protein expression associated with hepatic steatosis, inflammation and IRI.◦Glycomics: the liver perfusate glycome profile may form part of future functional criteria [78]. A recent study found that the abundance of a single glycan, agalacto core-alpha-1,6-fucosylated biantennary glycan (NGA2F) was significantly higher in the perfusate of livers that developed PNF. We will test this hypothesis in sequential perfusate samples.

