#### Intra-operative outcome assessment

Recipient blood samples (before and after transplant) and post-reperfusion liver biopsy (as well as bile duct biopsy where feasible) will be taken:◦ Peri-operative blood taken (before transplant) and re-perfusion (following liver transplantation)◦ Liver core biopsy taken post-reperfusion◦ Bile duct biopsy taken post-reperfusion where feasible i.e. if sufficient bile duct length

These samples will be taken to determine the severity of ischaemia–reperfusion injury and changes in mean arterial pressure will be recorded to assess for post-reperfusion syndrome:Histological and biochemical evidence of ischaemia–reperfusion injury (IRI) in recipient [70]:Cytokine profile implicated in liver transplantation including [70]: CXCl8/IL-8, IL-10, IL-2, TNF-a, IFN-γ, IL-13, IL-4, IL-1β, IL-17A and IL-6.Liver histology (formalin fixed paraffin embedded biopsy) [33]:Neutrophil infiltration and leucocytosis determined using haematoxylin and eosin (H&E) stainGlycogen depletion determined using periodic acid-Schiff (PAS) stainLipid peroxidation determined using 4-HNE (4-hydroxynonenal) stainBile duct histology (formalin fixed paraffin embedded biopsy) [71]:Evidence of stroma necrosis, extramural peribiliary glands (loss/injury to cells) and presence of vascular lesionsPost-reperfusion syndrome (PRS) [65], a decrease in mean arterial pressure (MAP) of more than 30% for more than 1 min during the first 5 min after reperfusion [65].

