An ITT analysis will be performed for the primary outcome and secondary (donor liver related) outcomes. Secondary (recipient) outcomes will be analysed using a mITT approach. This analysis will exclude livers perfused but not transplanted for any reason.

For the mechanistic work, measures will be compared before and after perfusion to assess for a change during machine perfusion. A paired *t*-test will be used to compare the means of these levels pre- and post treatment to determine whether any change is statistically significant. For all analyses with statistical testing, a *p*-value of < 0.05 will be used to determine statistical significance.

Full details of the statistical analysis plan will be made available on the ISRCTN registry webpage (ISRCTN 14957538: 10.1186/ISRCTN14957538).

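### The storage rule for liver biopsies, read literally, leaves one formalin segment per liver, but the planned formalin-fixed reperfusion-injury histology needs one at each of three timepoints

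*Protocol article*

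**What the plan says.** The section on collection and storage of biological specimens {33} sets the sampling: "A total of five core liver biopsies will be taken: two biopsies before perfusion, two at the end of perfusion and one following reperfusion". It continues: "Each liver biopsy will be divided into two segments". The storage rule follows: "Per liver, one segment will be stored in formalin and the remaining segments will be frozen". Bile duct samples, one per timepoint where feasible, are treated differently: "The bile duct biopsies will not be divided into two and only stored in formalin".

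Three other places depend on this tissue:

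- **Secondary outcome measures, histological and biochemical.** Liver histology for ischaemia-reperfusion injury (H&E, PAS and 4-HNE stains) is specified as formalin-fixed and paraffin-embedded. The timing is: "Biopsy samples collected pre-perfusion, post-perfusion and re-perfusion in the recipient (following liver transplantation".
- **Intra-operative outcome assessment.** The same fixation and the same three stains are repeated for the liver core taken after reperfusion.
- **Mechanistic studies outcome measures.** The first aim is: "Histological quantification of MaS measured pre-perfusion, post-perfusion and during re-perfusion in the recipient". No fixation method is named there.

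For the mechanistic work, the description of statistical methods {20a} says that "measures will be compared before and after perfusion to assess for a change during machine perfusion", using a paired t-test.

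**The concern.** A single formalin segment can represent only one timepoint, and the rule does not say which. If staff followed the sentence as it stands, the formalin-fixed reperfusion-injury histology could not be read at the three planned timepoints, and no liver would have a formalin-fixed pair of liver samples from before and after perfusion. The choice between formalin and freezing is made at collection, and the document describes no route from a frozen segment to the planned formalin-fixed sample. A mistake made at that moment would therefore be hard to recover.

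At stake is one group of secondary outcomes. The paired mechanistic comparison of steatosis is also at stake if it is read on formalin tissue.

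**Working it through.** This is a count; no sample-size formula applies.

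**Inputs, all from the specimen section {33} unless stated**
- Cores per transplanted liver: 2 before perfusion, 2 at the end of perfusion, 1 after reperfusion.
- Segments per core: 2.
- Formalin segments per liver, literal rule: 1.
- Timepoints for formalin-fixed reperfusion-injury histology: 3 (secondary outcome measures). A liver that is not transplanted has no reperfusion sample, so 2.
- Livers to be randomised: 60 (trial design).

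**The plan's own figure.** 2 + 2 + 1 = 5 cores, which agrees with the stated total.

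**Segments available.** Transplanted: 5 × 2 = 10. Perfused but not transplanted: (2 + 2) × 2 = 8.

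**Split under each reading of the rule**

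| Reading | Transplanted: formalin / frozen | Not transplanted: formalin / frozen |
|---|---|---|
| Literal, one per liver | 1 / 9 | 1 / 7 |
| One per timepoint | 3 / 7 | 2 / 6 |
| One per biopsy | 5 / 5 | 4 / 4 |
| Needed for the reperfusion-injury histology | at least 3 in formalin | at least 2 in formalin |

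The literal reading falls short by 3 − 1 = 2 segments per transplanted liver and 2 − 1 = 1 per liver not transplanted. Either of the other readings meets the need.

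**Across the trial.** If all 60 livers were perfused and fully sampled, the literal rule gives 60 × 1 = 60 formalin segments. The need is between 60 × 2 = 120 (none transplanted) and 60 × 3 = 180 (all transplanted). These are upper-end counts, because research biopsies before implantation are taken only with donor-family consent to research.

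**What is not touched.** Bile duct biopsies go into formalin undivided at each timepoint where one is feasible, so their series over time is kept. The primary endpoint rests on perfusion measurements at 6 h and uses no histology.

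**The case against.** The strongest reply is that this is a drafting slip whose meaning is clear. The preceding sentence concerns each liver biopsy, so the rule can be read as per liver biopsy: one half fixed, the other frozen. Halving all five cores in order to fix one segment of ten would make little sense, and the contrast with the undivided bile duct samples suggests that liver cores are divided so that part of each can be fixed. The outcome sections state the three-timepoint requirement plainly. The article also refers to a study manual and standard operating procedures, which are not shown and may be correct.

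Much of this stands. A slip is the likelier explanation, and the collection schedule itself yields enough tissue. It does not remove the contradiction, for two reasons. First, the text does not settle between per timepoint and per biopsy. The plural for the remaining segments sits poorly with a halved core, which leaves only one, while the wording used for bile duct samples (at each timepoint) was not used for liver cores. The two readings differ by two formalin segments per transplanted liver, and so in how much frozen tissue is left. Second, this is a stated handling rule, not a detail left out by condensing. If the manual differs, the article misreports it.

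A reader might infer something stronger: that the effect of defatting on macrovesicular steatosis cannot be estimated, or that the trial will have no paired formalin samples at all. The document supports neither. The mechanistic section says only that the steatosis assessment is histological, and frozen liver segments would exist at every sampled timepoint even under the literal rule. Bile duct tissue is kept in formalin throughout. A count of 0 of 60 livers with a formalin liver pair describes a literal worst case, not what sites are known to do.

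**Conclusion.** The storage sentence is wrong as written and contradicts the formalin-fixed, paraffin-embedded liver histology planned for ischaemia-reperfusion injury. The shortfall under the literal rule is 1 formalin segment against at least 3 for a transplanted liver, and 1 against at least 2 for a liver perfused but not transplanted.

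The conclusion rests on the literal wording, on full sampling at each timepoint, and on one formalin segment serving one timepoint. It is firm for the reperfusion-injury histology. For macrovesicular steatosis it is conditional on formalin tissue being used. Bile duct histology, the primary endpoint and the trial's power are unaffected. Actual practice may already follow a workable reading; the document does not show it.

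**What to change.** Reconcile the specimen section {33} with the secondary outcome measures and the intra-operative outcome assessment. Replacement wording could be: *At each timepoint (pre-perfusion, end of perfusion, post-reperfusion) at least one liver segment will be stored in formalin and the remaining segments will be frozen.* If sites already fix one segment per biopsy, say so and keep that, so that the correction does not reduce formalin tissue from five segments to three.

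Check that the study manual says the same. Recruitment was open at publication, with an anticipated end of 30 November 2024, so also check the samples stored so far and record how many livers have formalin liver tissue at each timepoint.

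The cost is one sentence and a sample audit, with no extra biopsy. Compared with the literal rule, a transplanted liver loses 9 − 7 = 2 frozen segments under one per timepoint, or 9 − 5 = 4 under one per biopsy. This matters for the tissue left for the mechanistic work.
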